#### Aim 1a: comparison of target mechanisms between Stepping Up and non-Stepping Up counties

##### Primary

We will test the hypothesis that Stepping Up counties will show faster rate of improvement in *the use of/ capacity for performance monitoring* (i.e., total scores on our Performance Monitoring measure) than comparison counties, using GLMM or GEE. Analyses will test for differences in slopes (rates of change). Separate secondary analysis will compare rates of change in the adapted Routine Decision-Making scale total score between Stepping Up and comparison counties.

##### Secondary

We will test the hypothesis that Stepping Up counties will show faster rate of improvement in the *use/functioning of interagency teams* (i.e., total scores on the integrated NCJTP Relationship Assessment Inventory-IOR measure) than control counties using the same statistical techniques. We will test the hypothesis that Stepping Up counties will show faster rate of improvement in *common goals and mission across agencies* (i.e., agreement between perceived agency and county priorities) than comparison counties using GLMM or GEE. We will conduct similar analyses of agreement among respondents within each county on the importance of mental health treatment for justice-involved individuals. We will test the hypothesis that Stepping Up counties will show faster rate of improvement in *system integration* (score of 6 or more on the Relationship Assessment Inventory score) using GEE. Separate secondary analysis will compare rates of change in the use of the same screening and assessment instruments by multiple agencies in Stepping Up and comparison counties.

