**Target implementation mechanisms**				
Use of/capacity for performance monitoring	Performance Monitoring measure (primary) Adapted Routine Decision-Making scale [37]	X X	X X	X X
Use and functioning of nteragency teams	Adapted NCJTP Relationship Assessment Inventory [38]	X	X	X
Common goals and mission across agencies	Adapted NCJTP Goals/Mission scale [38] (primary) Agreement (kappa) among respondents within counties on ratings of the importance of providing mental health treatment services for justice-involved individuals	X X	X X	X X
System integration (vs. single programs)	Use of same screening/assessment instruments across agencies in the county	X	X	X
	Total score of 18+ on the NCJTP Relationship Assessment Inventory [38]	X	X	X

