##### Use and functioning of interagency teams (agencies nested within counties)

To examine the activities and functioning of interagency teams, we integrated the NCJTP Relationship Assessment Inventory [38] with additional items based on the goals and priorities of Stepping Up. This integrated scale contains 18 items such as “we share general information about populations in need of treatment services” (0 = no, 1 = yes) with one point assigned for each collaborative activity across the other 3 agencies. The total score (up to 54) reflects joint activities among agencies.

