##### System integration (agencies nested within counties)

 is a dichotomization of the NCJTP Relationship Assessment Inventory [38] total score (i.e., excluding the additional items). Counties with scores of 18 or more are considered to have achieved “system integration”. A secondary (county level) measure will reflect the degree to which each of 12 listed behavioral health screening and assessment instruments are used by and/or shared among multiple responding agencies within a county. For each of the 12 instruments listed, counties will receive a score (0 = no agencies use the same instrument, 1 = two agencies use the same instrument, 2 = three agencies use the same instrument, and 3 = all four agencies use the same instruments).

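### The cut-off for the secondary binary endpoint system integration is 18 or more in the Measures section and Table 3, but 6 or more in the Aim 1a analysis

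*Protocol article*

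**What the plan says.** The protocol article gives the cut-off for system integration in three places.

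- **Measures, Aim 1, System integration.** The measure "is a dichotomization of the NCJTP Relationship Assessment Inventory [38] total score (i.e., excluding the additional items"; then "Counties with scores of 18 or more are considered to have achieved" integration.
- **Table 3, Target implementation mechanisms.** The indicator is "Total score of 18+ on the NCJTP Relationship Assessment Inventory".
- **Analysis plan, Aim 1a, Secondary.** The hypothesis of faster improvement is tested by GEE on a "score of 6 or more on the Relationship Assessment Inventory score".

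The scoring is described under Use and functioning of interagency teams. There the inventory is combined with additional items: "This integrated scale contains 18 items such as" sharing general information, scored no/yes, "with one point assigned for each collaborative activity across the other 3 agencies". The stated maximum of this combined scale is 54.

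Aim 1b, Secondary, then uses integrated systems of care as a mediator, taking its score from the measures already identified.

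**The concern.** The same construct on the same inventory has two thresholds. For a dichotomised score the threshold is the endpoint definition, so an analyst following the Measures section and one following the Aim 1a text could classify the same responses differently. The estimated difference in rates of change, and the mediation result that uses the same variable, could then depend on which section was followed. With both figures in print, either could later be cited as the prespecified one.

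The Aim 1a wording also leaves out the exclusion of the added items that the Measures section specifies. The scored item set is therefore not restated where the test is described.

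**Working it through.** **1. Scale arithmetic.** The stated maximum reproduces: 18 items × 3 partner agencies = 54. This belongs to the combined scale. System integration uses only the original inventory items. Their number, K, is not given, so the maximum of the dichotomised score is 3K with K unknown. A total of 18 is reachable only if 3K ≥ 18, that is, K ≥ 6.

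**2. Could the two cut-offs be the same rule?** 18 / 3 = 6, so a per-partner score is the natural candidate. Three versions are possible:

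| Reading of 6 | Example (points per partner) | Total | Same as a total of 18 or more? |
|---|---|---|---|
| At least 6 with every partner | 10 + 8 + 0 | 18 | No: meets 18, fails this rule |
| At least 6 with any one partner | 6 + 0 + 0 | 6 | No: meets this rule, fails 18 |
| Average of 6 across three partners | sum = 3 × 6 | 18 | Yes |

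Only the average is equivalent, and the article defines no per-partner or average score. Read as written, the Aim 1a text applies 6 to the inventory score itself.

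**3. How far apart could they be on one scale?** The documents give no score distribution, so this is an illustration only. Assume K original items, each asked about three partners, and each of the 3K answers independently yes with probability p. The share classed as integrated is then P(X ≥ c), with X ~ Binomial(3K, p) and c = 6 or 18.

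| K (assumed) | 3K | p (assumed) | Share at 6 or more | Share at 18 or more |
|---|---|---|---|---|
| 8 | 24 | 0.1 | 2.8% | 0.0% |
| 10 | 30 | 0.3 | 92.3% | 0.1% |
| 12 | 36 | 0.4 | 99.9% | 14.6% |
| 14 | 42 | 0.4 | 100.0% | 40.9% |
| 14 | 42 | 0.6 | 100.0% | 99.2% |

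The gap ranges from almost nothing, when endorsement is very low or very high, to more than 90 percentage points. The cut-offs are therefore not interchangeable, but the actual gap cannot be known from the article.

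**4. Where it reaches.** In the analysis plan, the Aim 1a primary test is performance monitoring and the Aim 2 primary test is the number of clients receiving services. The primary mediators in Aim 1b are the performance-monitoring scores. System integration is listed as secondary in both Aim 1a and Aim 1b. The power section does not refer to this cut-off.

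**The case against.** The strongest reply is that this is a slip with an obvious answer. Two of three statements agree, including the formal definition and the assessment table. The third is a parenthesis, and 6 × 3 = 18 suggests a figure left over from a per-partner or single-agency scoring. This stands in part: it makes 18 the better-supported reading. It does not remove the inconsistency, because the article describes no such scoring and the conflicting figure sits in the sentence that states the test.

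A reader might infer more than the documents support:

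- **That the study will test a different endpoint from the one it defined.** The construct and inventory are the same in all three places, and the figure of 6 may simply not have been updated. What is shown is an inconsistent cut-off.
- **That a cut-off of 6 produces a ceiling at Wave 1.** This needs a score distribution, which the article does not give. Under some assumptions both cut-offs classify nearly everyone alike.
- **That the main conclusions are at risk.** The study-aims section calls the comparison of mechanisms primary as a group, but the analysis plan names performance monitoring as the primary mechanism and places system integration under secondary analyses.
- **That a continuous analysis or a county aggregation rule is missing.** Aim 1a already compares rates of change in the combined inventory total. The Measures section labels system integration as agencies nested within counties. How several respondents' scores are combined is operational detail that an article may leave to a fuller plan.

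**Conclusion.** The inconsistency is real and should be fixed. One secondary binary endpoint has two cut-offs, 18 or more and 6 or more, in current text, and no stated scoring reconciles them. At least one place is wrong or refers to a score that is not defined. The ambiguity passes to the secondary mediation analysis of integrated systems of care. The primary mechanism, the primary outcome, the primary mediators and the power figures are unaffected.

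The conclusion rests on the quoted wording alone. The percentages in the table rest on assumed K and p and on independent answers; they show only that the two cut-offs can differ greatly on one scale. The explanation by partner scoring is inference.

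**What to change.** Before any outcome comparison, state one cut-off on one named score in all three places: Table 3, the Measures entry for system integration, and the Aim 1a secondary analysis. As 18 appears in both the formal definition and Table 3, change the Aim 1a text to 18 or more on the inventory total excluding the added items. If the investigators confirm that a per-partner score of 6 was intended, define it (every partner, any partner or the average) and change Table 3 and the Measures section to match. The secondary mediation analysis then takes the same definition.

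The cost is a few words of text and confirmation from the investigators. No new data or additional analysis is needed.

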#### Aim 1b: tests of mediation

##### Primary

We will test the hypothesis that *changes in use of performance measures* (i.e., scores on UPMDC and the adapted Routine Decision-Making scale) will mediate any differences found in *rates of change in primary measures of justice-involved clients receiving behavioral health services, number of EBPPs, and resources available*. These primary mediator analyses will use structural equation models, and path analyses.

##### Secondary

We will conduct a series of analyses examining changes in interagency teams, common goals and missions, and integrated systems of care using scores from respective measures identified above, as mediators of a number of justice-involved individuals receiving services, number of EBPPs available, and number of resources using appropriate baseline measures or months since joining Stepping Up as controls.

#### Aim 2: comparison of implementation outcomes between Stepping Up and non-Stepping Up counties

##### Primary

We will test the hypothesis that Stepping Up counties will show faster rate of improvement in the number of justice-involved clients receiving behavioral health services than will comparison counties, using GLMM and GEE. Analyses will test for differences in slopes (rates of change) between the two sets of counties.

##### Secondary

We will separately test the hypotheses that Stepping Up counties will show faster rate of improvement in the *number of behavioral health EBPPs available to* and *resources for behavioral health EBPP for justice-involved individuals* using GLMM, GEE, and GHLM.

We will examine moderators of the effects of Stepping Up participation on our primary outcome (justice-involved clients receiving behavioral health services) using structural equation models. A priori moderators include months between a county joining Stepping Up and study baseline, levels of implementation outcomes at study baseline, type of agency, organizational culture support for innovations (i.e., score on NCJTP Assess Your Organizational Culture scale [38]), jails with their own behavioral health staff, yes/no presence of legislative reforms, counties in states that have mental health diversion funding, and counties with divisions that provide cross-system trainings.

#### Aim 3: characterize implementation processes and critical incidents and assess counties’ fidelity to Stepping Up (quantitative)

We will examine the relationships between use of implementation strategies identified in the Implementation Strategy Checklist and faster rates of change in implementation outcomes, using GLMM and GEE while controlling for baseline measures and months since joining Stepping Up. We will use Bonferroni correction to control for multiple comparisons of implementation strategies (using the Checklist) for each of the three implementation outcomes.

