#### Aim 3: characterize implementation processes and critical incidents

##### Qualitative

We will use qualitative data to triangulate quantitative findings, enrich our understanding of how the target mechanisms work and lead to outcomes and critical incidents to EBPP implementation success or failure. Qualitative data will include interviews with 30 of the 475 county pairs (60 paired counties total). County pairs were randomly selected at Wave 1 (stratified by small, medium, and large county populations) and followed longitudinally at Waves 2 and 3. We anticipate 180 qualitative interviews (60 respondents at 3 time points). We will alternate CJ and behavioral health respondents to obtain multiple perspectives on the county’s progress. Respondents will be invited for interviews regardless of their survey status (i.e., completed, not yet completed, declined) for that wave.

*Fidelity to Stepping Up/Quantitative characterization of implementation strategies and sub-strategies used* to improve mental health or substance use services for justice-involved individuals and/or to reduce the number of people with mental illness in jail (agencies nested within counties). We will use a checklist with strategies and their descriptions constructed from the six main Stepping Up strategies as well as categories conceptualized by Powell [54] and the CJ-IIM [17]. Respondents will select whether anyone in the county is “planning to address this”, “some progress made”, or “significant progress made” using each strategy.

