### Power analyses

The expected sample (475 paired counties, up to 4 respondents per county, resulting sample size of ~ 3800) and the response rate of 50% gives an expected sample of 1900 respondents. Given that anywhere from 0 to 4 respondents may complete the survey in any given county, with a 50% overall response rate, we anticipate that 712 counties will have at least one respondent who completes the survey. We used a conservative (higher than expected) intraclass correlation coefficient of 0.1 for addressing clustering of agencies within counties.

For county-level analysis, an effect size of 0.2, power of 0.8, confidence level of 95%, and statistical significance level of 0.05 were used to calculate the minimum sample size. Repeated measures analysis required a minimum total sample size of 304 counties. For logistic regression and other nonlinear predictive models, depending on the type and quantity of variables used in the model, the minimum total sample size required varied between 156 and 489 counties. With attrition, our calculations showed a power of 0.9 and more for most county-level analyses.

For agency-level analysis, a conservative agency-level effect size estimate (*d* = 0.1), a power of 0.8, confidence level of 95%, and significance level of 0.05 were used to calculate the minimum required sample size. Repeated measures analysis comparing respondents from Stepping Up and comparison counties resulted in a minimum sample size of 524 respondents. When comparing the response measures, measured at the agency level, over time, a minimum sample size of 1200 respondents is required. For predictive logistic regression and other nonlinear predictive models, the minimum sample size varied between 673 and 1100 respondents. Given the larger sample size of this study, our calculations showed a power higher than 0.9 for agency-level analyses.

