### Analysis plan

#### General approaches

Primary tests will be 2-sided with α = 0.05. Analysis approaches accommodate nested and repeated measures data. We will examine predictive associations between Stepping Up membership, hypothesized target mechanisms, and implementation outcomes over time. We will use general linear models and generalized linear mixed models (GLMM) when the dependent variables are continuous and noncontinuous, respectively. GEE will be used instead when distributional assumptions are not met. For non-aggregated dependent variables reported at the agency level (i.e., hierarchical data), a random intercept growth hierarchical linear model (GHLM) will be fitted. All analyses will covary: (1) Wave 1 (baseline) values of dependent variables, (2) months since the county joined Stepping Up, (3) the matching score, (4) an indicator representing whether a the county shares their mental health administrator with other counties, and (5) a similar indicator for shared justice roles across counties.

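### Power for the Aim 3 strategy tests is not covered by the figures printed at alpha 0.05, and Holm's procedure would control the same error as Bonferroni without ever having less power

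*Protocol article*

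**What the plan says.** In the Analysis plan, the quantitative Aim 3 section relates use of each checklist strategy to rates of change in the implementation outcomes and sets the multiplicity rule: "We will use Bonferroni correction to control for multiple comparisons of implementation strategies (using the Checklist) for each of the three implementation outcomes". I read this as one family of strategy tests per outcome.

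The number of strategies is not given. Under Measures, Aim 3, the article says "We will use a checklist with strategies and their descriptions constructed from the six main Stepping Up strategies", and adds categories from two further sources. Six is therefore a floor.

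The Power analyses section sets the agency-level calculation at "a conservative agency-level effect size estimate (*d* = 0.1), a power of 0.8, confidence level of 95%, and significance level of 0.05". It expects 1,900 respondents: "the response rate of 50% gives an expected sample of 1900 respondents". It prints several agency-level minima: 524 for the repeated-measures comparison of the two county groups, 673 to 1,100 for logistic and other nonlinear models, and, for change over time, "When comparing the response measures, measured at the agency level, over time, a minimum sample size of 1200 respondents is required". It concludes "Given the larger sample size of this study, our calculations showed a power higher than 0.9 for agency-level analyses". The county-level conclusion is softer: 0.9 or better for most analyses. No corrected alpha appears in the section.

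The aims section describes the strategy analysis as exploring which strategies lead to better outcomes.

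**The concern.** The agency-level power sentence has no exception, yet the Aim 3 strategy tests are not judged at the alpha behind it. A reader who applies the printed power to Aim 3 would expect a real association of the planned size to be missed less than 10% of the time. On some of the printed minima the chance of missing it is nearly double that or more. A strategy without a significant association could then be taken as well tested and found to have none.

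Separately, single-step Bonferroni gives up power that can be kept. Holm's procedure controls the same family-wise error under any dependence between the tests, uses the same p-values, and rejects everything that Bonferroni rejects.

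**Working it through.** **Inputs.** From Power analyses: alpha 0.05, power 0.8, N = 1,900 respondents, 712 counties with at least one respondent, agency-level minima N0 of 524, 673, 1,100 and 1,200, and county-level minima of 304 (repeated measures) and up to 489 (nonlinear models). Two-sided testing is stated for primary tests ("Primary tests will be 2-sided with α = 0.05") and assumed here for Aim 3. The number of strategies k is at least 6; larger values are assumptions.

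**Formula.** A minimum N0 for 80% power at two-sided 0.05 fixes the noncentrality at 1.960 + 0.842 = 2.802. At sample size N it becomes 2.802 × √(N/N0). Power = Φ(noncentrality − z), with z the two-sided critical value at 0.05/k.

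**The plan's own figure first.** N0 = 1,200: 2.802 × √(1900/1200) = 3.53, and Φ(3.53 − 1.96) = 0.94. The other three minima give more, so the statement of power above 0.9 reproduces at alpha 0.05 if the minima are accepted.

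**Corrected alpha.** For k = 6, alpha = 0.0083 and z = 2.64. With N0 = 1,200, Φ(3.53 − 2.64) = 0.81. Agency level, N = 1,900:

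| Minimum N0 | alpha 0.05 | k = 6 | k = 10 | k = 18 | k = 30 |
|---|---|---|---|---|---|
| 1,200 | 0.94 | 0.81 | 0.76 | 0.70 | 0.65 |
| 1,100 | 0.96 | 0.85 | 0.81 | 0.76 | 0.70 |
| 673 | 0.997 | 0.98 | 0.97 | 0.96 | 0.94 |
| 524 | 0.9996 | 0.997 | 0.994 | 0.990 | 0.986 |

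County level, N = 712: the 304 minimum gives 0.99 at 0.05 and 0.95 at k = 6; the 489 minimum gives 0.92 and 0.77.

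**Sensitivity on the 1,200 basis.** If the minima do not already include the intraclass correlation of 0.1, the design effect is 1 + (1900/712 − 1) × 0.1 = 1.167 and the effective N is 1,628. Power is then 0.90 at 0.05 and 0.73 at k = 6. With an assumed 20% loss of respondents (N = 1,520) it is 0.88 and 0.70.

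**Holm against Bonferroni.** Simulation with 200,000 runs, noncentrality 3.53 for each real effect, and test statistics independent or correlated at 0.5. Average power per real effect:

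| k | Real effects | Bonferroni | Holm |
|---|---|---|---|
| 6 | 1 | 0.81 | 0.81 |
| 6 | 3 | 0.81 | 0.84 |
| 6 | 6 | 0.81 | 0.90 to 0.92 |
| 18 | 1 | 0.70 | 0.70 |
| 18 | 9 | 0.70 | 0.74 to 0.75 |
| 18 | 18 | 0.70 | 0.82 to 0.86 |

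Holm's simulated family-wise error stayed below 0.05 wherever some strategies had no effect.

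**The case against.** Bonferroni is valid, and choosing it is not an error. The analysis is exploratory, and the power section never mentions the checklist. A condensed article may leave corrected-alpha power for such an aim to a fuller document. All of this stands, and it limits the point to a qualification and a better procedure.

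A reader might infer that the plan's own figures put Aim 3 power at 0.81 or less. The documents do not support that:

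- The article ties no minimum to Aim 3. The 1,200 figure is the closest match, because it concerns agency-level measures over time, but the match is the reader's. On the 673 and 524 minima power stays above 0.9 for every k shown.
- The noncentrality is borrowed. Strategy use is a graded response of unknown prevalence, and no effect size is stated for it.
- Under the definitions in Measures, only the resources outcome is labelled agency level. Clients served is labelled agencies nested within counties, and the count of available practices is county level, where the power claim is already hedged.
- At k = 6 on the 1,200 basis, 0.81 still meets the 0.8 target used for sizing.

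It can also be said that Holm's gain depends on how many strategies really matter. That is true: with one real effect there is no gain. But there is never a loss of power, so an uncertain gain is no reason to prefer Bonferroni. What remains true without exception is that the power statements were computed at 0.05 and the Aim 3 tests are not run at 0.05.

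**Conclusion.** The point holds in a limited form. The printed power figures belong to tests at alpha 0.05 and cannot be applied to the corrected Aim 3 strategy tests. With six strategies, agency-level power ranges from about 0.81 to above 0.99 depending on which printed minimum applies; on the 1,200 and 1,100 minima it falls below the stated 0.9. More strategies lower it further.

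These figures rest on the minima taken at face value, a full 1,900 respondents, two-sided tests, and strategy effects as detectable as those behind the minima. The minima could not be confirmed: 524 does not follow from d = 0.1 by a two-means formula (3,140 in total), and 1,200 cannot be tied to one formula because the within-unit correlation is not stated. The figures show that the claim does not transfer; they do not establish the power of Aim 3.

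Holm is the better choice on general grounds that need none of these assumptions. Only the size of its gain depends on them. No primary test is affected.

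**What to change.** In the quantitative Aim 3 section of the Analysis plan, replace Bonferroni with Holm's step-down procedure over the checklist strategies, within each of the three implementation outcomes as now. With k strategies, order the p-values from smallest to largest, compare the j-th with 0.05/(k − j + 1), and stop at the first that fails.

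In Power analyses, say that the agency-level and county-level statements of power around or above 0.9 apply to tests at alpha 0.05 and not to the multiplicity-corrected Aim 3 strategy tests. Give power for those tests only once the actual number of strategies and the applicable minimum sample size are fixed. The values worked out here should not be printed as the plan's power.

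The cost is wording: the same p-values, no extra data and no change to any primary analysis. There are two downsides. Simultaneous confidence intervals are less simple under Holm than under Bonferroni, and the power stated for Aim 3 may look less favourable.
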